### Study visits

Seven study visits per subject will be scheduled in the study as follows: pretreatment visit (Day − 14 to Day 0), treatment visit (Day 1), discharge visit (on the day of discharge from hospital), follow-up visit month 1 (Month 1 post-treatment), follow-up visit month 3 (Month 3 post-treatment), follow-up visit month 6 (Month 6 post-treatment) and follow-up visit month 12 (Month 12 post-treatment). These visits will be made at the patient ward before discharge or study site office after discharge. At scheduled visits, data relating to demography, operation duration, estimated blood loss during operation period, length in days of the stay at hospital, and perioperative complications, visual analogue scale (VAS) pain score and lumbar Japanese Orthopaedic Association (JOA) score, concomitant medication, new-onset adverse events, etc. will be collected. See Fig. 1 for more details.

In case severe adverse events occur, the subjects can decide to drop out any time during the study.

### Outcome measures

#### Primary outcome

The primary outcome endpoint is the new-onset lower extremity neurological symptoms, including new adverse events of pain, numbness, and foot drop at different severity, which occur on the day of surgery performed until prior to discharge from hospital. In order to exclude the influence of nerve root edema, these new-onset symptoms to be included for analysis should not be significantly relieved three days after conservative treatment of nerve dehydration.

#### Secondary outcomes

The efficacy endpoints in this study mainly included VAS pain score, and lumbar JOA recovery rate pre and post LIF surgery. The VAS pain score is an ordinal scale of 0 to 10 points, with 0 indicating no pain, a higher value indicating more severe pain, and 10 indicating the most severe one. The lumbar JOA recovery rate is derived from lumbar JOA score per subject visit. Lumbar JOA score involves four aspects: subjective symptoms (a range of 0 to 9 points), clinical signs (a range of 0 to 6 points), daily life activities (a range of 0 to 14 points), and bladder function (a range of -6 to 0 points). The total JOA score ranged from − 6 (worst) to 29 points (normal), with a lower score indicating more significant dysfunction. The recovery rate of lumbar JOA is calculated by Hirabayashi’s method [20]as follows:

$$\mathrm{JOA}\;\mathrm{recovery}\;\mathrm{rate}=\frac{\mathrm{Post}\;-\;\mathrm{Preoperative}\;\mathrm{lumbar}\;\mathrm{JOA}\;\mathrm{score}}{29\;-\;\mathrm{Preoperative}\;\mathrm{lumbar}\;\mathrm{JOA}\;\mathrm{score}}\times\;100\%$$

#### Safety outcomes

The safety outcome endpoints also include other adverse events (AEs), surgery complications and laboratory tests as appropriate. The AEs profile of both treatments will be evaluated by examining the incidence of AEs according to the National Cancer Institute Common Terminology Criteria for Adverse Events (NCI CTCAE, Version 5.0, https://ctep.cancer.gov/protocoldevelopment/electronic_applications/docs/CTCAE_v5_Quick_Reference_8.5x11.pdf
).

### Sample size calculation

We used SAS^®^software, V.9.4 (SAS Institute, North Carolina, USA) to estimate sample size. According to the principle of outcome superiority design, the significance level α was set as 0.05 at two-sided. And the effect size indicates the treatment difference of clinical significance. The primary endpoint is the new-onset neurological symptoms (including pain, numbness and foot drop) of the lower limbs during the perioperative period from LIF surgery until discharge from hospital.

Assuming that the incidence of new-onset lower extremity neurological symptoms before and after the expected improvement [11]was 16% and 5%, respectively, when the two groups with a sample size of 242 subjects are randomly allocated in a 1:1 ratio, a power of 80% to establish superiority of modified LIF sequence over conventional LIF sequence will be reached. If the drop-out rate is 5% or less, a total of 254 eligible subjects would be required to randomly enroll in this study.

### Statistical analysis

The study includes two analysis populations. Of them, Safety set (SS) is defined as all subjects who have received the treatment of the study-specified operation (regardless of whether they participate in the randomized assignment or not) and will be the primary analysis population for safety data. The subjects in SS will be grouped according to the actual surgical treatment received. On the other hand, we will use full analysis set (FAS) for the baseline and efficacy data; It includes all subjects who are randomized into the study groups and received the study operation scheme. Following the principle of intention to treat, subjects in FAS would be analyzed by their randomly assigned group, regardless of the actual operation received.

The primary endpoint in this study is new-onset lower extremity neurological symptoms. The Cochran mantel Haenszel (CMH) method stratified by random stratification factors as appropriate will be used to test the statistical hypothesis. The incidence and 95% confidence interval (CI, Clopper-Pearson method) of will be estimated by treatment group. The CI of incidence difference between the two groups will be obtained by Newcombe method [21]. Similar statistical analysis will further be carried out for individual events of new-onset lower limb neurological symptoms, or Fisher exact method as appropriate will be used for comparison between groups. Additionally, similar analysis for the relief of old lower extremity neurological symptoms will be conducted for pooled and individual events, namely pain, numbness and foot drop during the perioperative period.

For VAS pain score, we will use analysis of covariance (ANCOVA) to compare the between-group changes of the observed values from baseline values after treatment. The random stratification factors as appropriate and the treatment group will be considered as fixed factors with the baseline value as covariate. The least squares mean (LSM), the difference from the control group and its 95% CI will be also provided. Similarly, 3-month recovery rate of lumbar JOA will be analyzed with the use of ANCOVA method.

In addition, we will use a repeated measures mixed effects model (MMRM) as supportive analysis as appropriate. MMRM analysis has treatment group, time and time treatment group interaction as fixed effects, baseline value as covariate, and subjects as random effects. When missing data occur, the last observation carry forward method (LOCF) will be applied to primary analysis and no data imputation as sensitivity analysis. If data distribution limits the use of ANCOVA, a rank-based analysis will be utilized. The LSM, the difference from the control group and its 95% CI will be also provided.

In this study, we will use a *p*-value of 0.05 or less at two-sided to indicate significance for any statistical tests with the use of R, V.4.0.4 [22] and SAS^®^ software, V.9.4 (SAS Institute, North Carolina, USA).

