## Introduction

Lumbar spinal stenosis (LSS) may lead to severe pain in low back or leg and also neurogenic claudication [1]. In clinical practice, the lumbar interbody fusion (LIF) technique has been widely used in the treatment of LSS patients to restore the height of the intervertebral disc and foramen and also the sagittal volume of the lumbar spinal canal [2].

In recent years, however, the postoperative neurological symptoms after LIF surgery, characterized by new-onset postoperative pain or numbness, dysesthesia, and muscle weakness have aroused widespread concern among clinicians [3–7]. Although these symptoms are usually transient and would be significantly relieved by themselves, it has a great impact on the quality of life of patients at that time interval. Some researchers have hypothesized about what causes these symptoms. Postigo et al [8]reported an increased risk of numbness, pain, and even foot drop after over-distraction on LIF surgery. A study by Matsui et al [9]showed that during the process of nerve root being pulled, the nerve root usually has ischemia, and hence the traction pressure and duration may be the potential risk factors for nerve root injury. Fu et al [10] found that when the height of the intervertebral space was increased to 140% of the original height, the nerve root tension increased the risk of injury significantly.

These findings coincide with our clinical experience in recent prospective research [11]. In this prospective observational clinical trial, we observed that fixation followed by fusion implantation resulted in a more physiologic reconstruction of the intervertebral space height, rather than excessive distraction resulting in excessive tension of the walking nerve roots, and reduced the incidence of postoperative neurological symptoms. It is essential to acknowledge that previous studies have concluded that additional fusion in conjunction with decompressive surgery may not yield discernible benefits, furthermore, they have noted potential drawbacks such as increased hospitalization time and blood loss [12–14]. The pressing challenge, therefore, lies in the quest to enhance the outcomes of LIF surgery. By doing so, we can bridge the gap between fusion and non-fusion surgery, catering to the unique needs of patients who may still require fusion surgery, and offering a more tailored approach that optimizes the surgical outcomes.

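### Read literally, the supportive MMRM is a random-intercept model with one variance for all visits, so its visit-specific intervals are miscalibrated if the variance of VAS or JOA recovery changes over follow-up (minor).

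*Protocol article*

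**What the plan says.** All references are to the protocol article.

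- **Role of the model** (Statistical analysis): "we will use a repeated measures mixed effects model (MMRM) as supportive analysis as appropriate".
- **Terms of the model** (same section): "MMRM analysis has treatment group, time and time treatment group interaction as fixed effects, baseline value as covariate, and subjects as random effects". No baseline-by-time term is listed. The residual covariance is not mentioned.
- **Main analyses of the same endpoints** (same section): for VAS, "we will use analysis of covariance (ANCOVA) to compare the between-group changes of the observed values from baseline values after treatment"; for JOA, "3-month recovery rate of lumbar JOA will be analyzed with the use of ANCOVA method". The primary endpoint is tested by a CMH method.
- **Missing data** (same section): LOCF for the primary analysis, with an analysis without imputation as sensitivity analysis. Least squares means, differences and 95% intervals are promised.
- **Visits** (Study visits): "Seven study visits per subject will be scheduled in the study as follows". The post-operative ones are discharge, Months 1 and 3, and then "follow-up visit month 6 (Month 6 post-treatment) and follow-up visit month 12 (Month 12 post-treatment".

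**The concern.** A random subject effect with independent residuals is compound symmetry. It assumes that scores are equally variable at discharge and a year later, and that discharge correlates with Month 12 as strongly as with Month 1. The single baseline covariate also assumes that the preoperative score predicts every visit equally well.

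Equal variance is a doubtful default for a 0 to 10 pain score followed from a few days after surgery to 12 months. The Introduction says of the new-onset neurological symptoms that "these symptoms are usually transient and would be significantly relieved by themselves". That sentence is about whether symptoms resolve, not about the variance of VAS or JOA recovery. It makes a change in spread plausible and does not establish one.

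At stake is the calibration of the treatment difference at single visits. With complete data the model gives every visit the same pooled standard error. Where the true variance is above the average the interval is too short, and where it is below the average the interval is too long.

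**Working it through.** **Plan's own figure.** The document gives no figure for this model. The only one needed is the number per arm. With 16% versus 5%, two-sided α 0.05, 80% power and pooled variance:

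n per arm = [1.960·√(2·0.105·0.895) + 0.842·√(0.16·0.84 + 0.05·0.95)]² / 0.11² = 120.7, rounded up to 121.

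That is 242 in total, as stated. It rests on the binary endpoint and does not depend on the point made here.

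**Inputs.** From the document: 121 per arm, five post-operative visits (discharge, Months 1, 3, 6, 12), 95% intervals. Assumed, because the document gives no value: the SD at each visit (after baseline adjustment), the correlations and the baseline slopes.

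**Formula.** With complete data, leaving the baseline adjustment aside, the estimated difference at visit t is the difference in visit means.

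- True SE at visit t: √(2σ_t²/n)
- SE from the random-intercept model: √(2σ̄²/n), where σ̄² is the mean of the visit variances
- Coverage at visit t: 2Φ(1.96·σ̄/σ_t) − 1

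**Worked case, SD falling 2.0, 1.8, 1.6, 1.4, 1.2.** σ̄² = (4.00 + 3.24 + 2.56 + 1.96 + 1.44)/5 = 2.64, so σ̄ = 1.625. The model SE is √(2·2.64/121) = 0.209 at every visit. The true SE is √(2·4.00/121) = 0.257 at discharge and √(2·1.44/121) = 0.154 at Month 12.

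- Discharge: 2Φ(1.96·1.625/2.0) − 1 = 88.9%
- Month 12: 2Φ(1.96·1.625/1.2) − 1 = 99.2%

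**Coverage by visit under a range of assumptions (same formula)**

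| Assumed SDs | Discharge | Month 1 | Month 3 | Month 6 | Month 12 |
|---|---|---|---|---|---|
| Equal | 95.0% | 95.0% | 95.0% | 95.0% | 95.0% |
| 1.8 falling to 1.4 | 92.0% | 93.6% | 95.1% | 96.4% | 97.5% |
| 2.0 falling to 1.2 | 88.9% | 92.3% | 95.3% | 97.7% | 99.2% |
| 1.8 rising to 2.2 | 97.1% | 96.1% | 95.1% | 93.9% | 92.6% |
| 1.5 rising to 2.5 | 99.2% | 97.7% | 95.3% | 92.3% | 88.9% |

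If only discharge, Month 1 and Month 3 enter the model (SD 2.0, 1.8, 1.6), coverage is 92.3%, 95.1% and 97.3%.

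**Which assumption does the damage.** A simulation of complete data (121 per arm, five visits, 4,000 data sets per scenario, random intercept and common baseline slope) separates the three restrictions:

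- Equal SDs, AR(1) correlation 0.6: coverage 94.6% to 95.4%. Unequal correlation alone does no harm.
- Equal SDs, baseline slope falling from 0.8 to 0.2: 94.5% to 95.7%. A common slope alone does almost none.
- SD rising 1.5 to 2.5, AR(1) correlation 0.6: 99.2% at the first visit down to 89.1% at the last, in agreement with the formula.

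Unequal variance is therefore the driver. None of this covers missing visits.

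**The case against.** The strongest reply is that the article does not state the residual covariance. It calls the model an MMRM, and the covariance structure is commonly left to a SAP, which is not shown. This stands in part. A reader might infer that the plan rules out any other covariance and that its intervals will be wrong. The document supports neither: it does not say that the random subject effect is the only covariance component, and it gives no variances by visit. But it is not merely silent. It lists the terms of the model, and the one within-subject term it lists is a random subject effect. A programmer who follows it literally fits a random intercept.

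A reader might also infer that the flaw undermines the only analysis free of LOCF. It does not, because the same section names an analysis without imputation. With missing visits a wrong correlation structure could matter in a likelihood model, but that is not quantified here, and the planned dropout is only 5%.

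Two further limits are fair. The article does not say which visits or which contrast the model will report. For a difference averaged over all visits, with complete data, the random-intercept standard error is correct even when variances differ. And the Relevance and dissemination section speaks of about three months of follow-up, against 12 months under Study visits; over the shorter span the effect is smaller.

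**Conclusion.** The point holds conditionally and is minor. As worded, the model amounts to compound symmetry with a common baseline slope. Visit-specific 95% intervals are then miscalibrated if, and to the extent that, the variance differs between visits. Under the assumed patterns, coverage at the most variable visit lies between about 89% and 93%, and at the least variable visit between about 97% and 99%. It stays near 95% in the middle of follow-up, which includes Month 3, the time point named for the JOA analysis. With equal variances nothing is wrong.

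These figures rest on assumed SDs, complete data and independent residuals around the subject effect. The model carries no main inference, and no stated sample size or power figure changes.

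**What to change.** In the model sentence, replace the random subject effect with an unstructured within-subject covariance across the post-operative visits. Name Kenward-Roger degrees of freedom and a fallback order if the model does not converge, for example heterogeneous Toeplitz and then compound symmetry with a sandwich variance. A baseline-by-visit term is optional good practice; the check above gives no strong reason to insist on it.

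The cost is one sentence and a changed model statement. Five visits need 5·6/2 = 15 covariance parameters in place of two, which about 240 patients support easily. In large samples the visit-specific intervals then return to about 95% whatever the variance pattern.

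### For the secondary VAS and JOA endpoints, LOCF is the main missing-data method and the planned MMRM is only supportive; the order should be reversed

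*Protocol article*

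**What the plan says.** All of this is in the protocol article, under Statistical analysis unless noted.

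- **Main VAS model.** The sponsor writes "we will use analysis of covariance (ANCOVA) to compare the between-group changes of the observed values from baseline values after treatment". On the model terms it adds "The random stratification factors as appropriate and the treatment group will be considered as fixed factors with the baseline value as covariate".
- **JOA.** "3-month recovery rate of lumbar JOA will be analyzed with the use of ANCOVA method".
- **MMRM.** Its rank is given as "we will use a repeated measures mixed effects model (MMRM) as supportive analysis as appropriate". Its terms are "MMRM analysis has treatment group, time and time treatment group interaction as fixed effects, baseline value as covariate, and subjects as random effects". The randomisation factors (single or multiple segments; modified Schizas B or C/D) are not among them.
- **Missing data.** "the last observation carry forward method (LOCF) will be applied to primary analysis and no data imputation as sensitivity analysis". No reason for choosing LOCF is given.
- **Withdrawal (Study visits).** "In case severe adverse events occur, the subjects can decide to drop out any time during the study".

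The missing-data sentence stands between the MMRM description and the rank-based fallback for the ANCOVA. I therefore read its primary analysis as the main analysis of VAS and JOA, not the analysis of the primary endpoint.

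**The concern.** LOCF assumes that a patient's score stays flat after the last visit attended. The Introduction describes new postoperative symptoms as mostly transient and self-resolving, which points the other way. A discharge score used as a Month 3 score then records the patient as worse than expected and treats that value as observed.

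This does little harm under the null if both arms lose patients at the same rate and time, but nothing in the design ensures that. The trial is open-label, patients may withdraw after severe adverse events, and the sample size section assumes that new neurological symptoms differ between arms (16% against 5%). The arm that loses more patients, or loses them earlier, looks worse for that reason alone. If that is the conventional arm, the error favours the modified sequence; if it is the modified arm, a real benefit is diluted.

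An MMRM on observed data needs only that missingness depends on what has been observed. It is already in the plan, ranked second.

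**Working it through.** **Inputs from the protocol article:** 242 evaluable and 254 randomised patients in a 1:1 ratio, dropout of 5% or less, two-sided α 0.05, ANCOVA with strata and baseline, JOA recovery rate at 3 months.

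**Assumptions, not in the document:** VAS means 6.5, 4, 3 and 2 at baseline, discharge, Month 1 and Month 3; SD 2; correlation 0.5 between visits; a stratum effect of 0.5; the split of dropout between arms. Each simulation used 127 patients per arm and 4,000 runs.

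**1. The plan's own figure.** Using pooled variance without continuity correction, n per arm = [1.960·√(2·0.105·0.895) + 0.842·√(0.16·0.84 + 0.05·0.95)]² / 0.11² = 120.7, so 121 per arm and 242 in total, with power 80.1%. Then 242/0.95 = 254.7, against the stated 254. The stated size is reproduced to within one patient. It rests on the binary in-hospital endpoint, so the VAS/JOA missing-data rule does not enter it.

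**2. Bias of LOCF with no true effect.** False difference = (dropout rate in one arm − dropout rate in the other) × (mean improvement still to come after the carried value). From discharge to Month 3 the assumed improvement is 4 − 2 = 2 points; from Month 1 it is 3 − 2 = 1 point; with half of the dropouts at each visit it averages 1.5.

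**3. Splits that keep overall dropout at the planned 5%.**

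| Dropout by arm | Formula, 1.5 points to come | Formula, 2 points to come | Simulated false difference | Type I error, LOCF-ANCOVA |
|---|---|---|---|---|
| 5% vs 5% | 0 | 0 | about 0 | about 5% |
| 2.5% vs 7.5% | 0.05 × 1.5 = 0.075 | 0.05 × 2 = 0.10 | 0.08–0.11 | 6–7% |
| 0% vs 10% | 0.10 × 1.5 = 0.15 | 0.10 × 2 = 0.20 | 0.15–0.20 | 11–14% |

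The lower ends are for dropout unrelated to the score and spread over discharge and Month 1. The upper ends arise when dropouts are all last seen at discharge, or when high discharge scores make dropout more likely. Simulation error on the type I error is about one percentage point.

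**4. Other methods on the same data.** With dropout depending on the discharge score, the false differences were:

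| Dropout by arm | LOCF | Observed cases | MMRM-type likelihood estimate |
|---|---|---|---|
| 2.5% vs 7.5% | 0.10 | −0.03 | 0.00 |
| 0% vs 10% | 0.20 | −0.06 | 0.00 |

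Adding a stratum term to the likelihood estimate changed neither its bias nor its standard error to two decimals.

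**5. JOA recovery rate, by the same formula.** If 10 to 40 percentage points of recovery are still to come, a 5-point dropout gap gives 0.05 × 10 = 0.5 to 0.05 × 40 = 2 percentage points; a 10-point gap gives 1 to 4.

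**6. With a true effect.** For a VAS benefit of 0.8 and 0% vs 10% dropout, the larger loss being in the arm that benefits, LOCF should give 0.80 − 0.10 × 1.5 = 0.65. The simulation gave 0.65, with power 83% against 95% for observed cases.

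**The case against.** The strongest reply is that little is at stake. At 5% overall dropout the distortion is 0.1 to 0.2 points on a 0–10 scale, it needs unequal dropout, and both a no-imputation sensitivity analysis and an MMRM are planned and would show a discrepancy. The article also gives no VAS or JOA trajectory, so the improvement still to come is assumed. All of that stands and makes this a modest point. What does not follow is that the ranking is immaterial: if the analyses disagree, the plan gives precedence to the one with the least plausible assumption.

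Several stronger readings are tempting but not supported:

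- **A large type I error.** A reader might infer 15% or 28% by supposing dropout of 5% vs 15% or 5% vs 20%. Those average 10% and 12.5%, above the planned 5%. A 15-point gap also exceeds the whole assumed difference in new symptoms, 16% − 5% = 11 points.
- **Dropout driven by the primary outcome.** The withdrawal sentence concerns severe adverse events, whereas the primary outcome counts symptoms of any severity. Unequal dropout is possible, but the document does not show it to be likely.
- **The missing strata cause the bias.** They do not (step 4). Their absence from the MMRM is only an inconsistency with the ANCOVA.
- **Equal correlation across visits.** The article names no within-subject covariance structure, and a condensed article may leave that to the analysis plan.
- **LOCF understates uncertainty.** With equal dropout the type I error stayed near 5%, so the calculations do not show this.

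**Conclusion.** The point holds as a low-cost improvement to the secondary analyses. LOCF is a poor main method for scores expected to keep improving, and the plan already contains a better one. Within the planned dropout, the false VAS difference is about 0.1 points with 6–7% type I error for a moderate imbalance, and 0.15–0.20 points with 11–14% when every dropout falls in one arm. It is zero under no true effect when dropout is equal. These sizes rest on the assumed trajectory, SD, correlation and dropout split; the direction of the error rests only on scores still improving and dropout differing by arm.

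A reader might infer that the trial's main conclusion is at risk. It is not: the primary endpoint is a binary event recorded before discharge and tested by CMH, and neither it nor the sample size depends on carrying VAS or JOA scores forward.

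**What to change.** 1. Make the MMRM on observed data the main analysis of VAS and JOA, and take the treatment contrast at a named visit (Month 3 for JOA; state the visit for VAS).
2. Move LOCF-ANCOVA to sensitivity.
3. As a side point, add the two randomisation factors to the MMRM so that it matches the ANCOVA. This is for consistency and will not alter the bias.

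The cost is a change of wording and a small amount of extra modelling work, since the model is already planned. The article reports that recruitment has not begun, so the change can be made before any outcome is seen. Continuing to collect scores from patients who leave after an adverse event would reduce the problem at source, but that changes trial conduct, needs follow-up effort, and is a separate decision from this one.
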